**Fig. 2 Fig2:**
[figure not shown]
Activity schedule that may occur during each contact with the participant

To ensure the traceability of the treatments, a systematic record of the name of the pharmaceutical preparation, and the quantity and lot number dispensed to each subject are maintained in the corresponding data collection book. The data are updated according to the standard working procedures (SWPs) for the preparation and control of 500-mg metformin tablets and according to the SWPs for the control of pills, which are provided by the Hospital Pharmacy Department.

At the first visit, an extensive history is obtained. The duration of pregnancy, birth weight, neonatal feeding, use of medication, tobacco and alcohol, and the presence of maternal gestational diabetes are reported. Regarding family history, data on hypertension, obesity, hypercholesterolemia, cardiovascular disease, and *diabetes mellitus* in first-degree (parents) and second-degree (grandparents) family members are collected. Girls are asked whether and when they experienced menarche. The parental education level is recorded, as well as height and weight.

### Adverse effects and co-medication

To assess the safety of metformin administration, the primary evaluation criteria are the absence of the adverse effects (AEs) described. The patients are assessed regarding all symptoms at each visit to identify potential AEs and the use of co-medication in the previous two months. A contact number is provided to enable enquiries regarding any symptom perceived as adverse. At this number, the patient is informed about what to do in the event of an adverse reaction. They are also requested to suspend the medication. The following information is recorded: description, date of onset and end date, severity, assessment of relation to the study medication, other suspect drug or device and action taken. Follow-up information should be provided as necessary. The prominent AEs are as follow: diarrhea, nausea, blood in the stools, headache, dizziness, general discomfort, sleepiness, cold or flu, pharyngitis, otitis, allergic episode, lactic acidosis, urea increment, hypercreatininemia, hypertransaminasemia and vitamin B_12_ deficiency, as well as any other symptoms reported by the participants. The relationships of the AEs to the study medication will be assessed by a qualified medical investigator.

### Physical examination

The Clinical Units conduct a complete medical examination, which is performed with pubertal assessment. Measurements of arterial BP, calibrated by hand and in duplicate, and heart rate are obtained with the subjects in a seated position using a cuff appropriate for the arm circumference. The average BP values are expressed in mmHg, and the percentiles are determined and adjusted for sex and age according to the chart published by the National Heart, Lung and Blood Institute.

At every visit, an extended physical examination is performed by the research physician. This examination includes auscultation of the heart, lungs and abdomen and also abdominal palpation. Clinical signs may be identified, including the presence of acanthosis nigricans, hypertrichosis, striae, acne, adipomastia or hypogonadism.

### Monitoring of lifestyle

The dietician centers administer a FFQ and a physical activity survey to all participants at the beginning and at the end of the trial. Both questionnaires have been normalized by the IDEFICS and HELENA European Projects [26] and validated by the CTS-02203 Excellence Project of the Regional Government of Andalucía. The HELENA Study developed and tested a questionnaire for use among adolescents, based on the long format of the International Physical Activity Questionnaire (IPAQ) [27], which provided internationally comparable data [28].

### Blood, urine and fecal sampling

General biochemical analyses are performed at the participating hospitals following internationally accepted protocols.

Blood samples are obtained for biochemical and hematological screening tests between 08.30 and 10.30. Three milliliters of blood are collected at the beginning and at the end of the trial. The blood is drawn via the antecubital vein. Peripheral white blood cells (buffy coat) are taken for deoxyribonucleic acid (DNA) extraction. Moreover, a 1-ml urine sample is obtained for oxidation marker analysis. Children should not eat for 12 hours before the sampling. All samples are collected and stored frozen by the research staff. The samples will be analyzed in the clinical laboratory of each hospital, as well as the INYTA.

In order to studying the childrens’ gut microbiota, 100–200 g of fecal sample is collected in a sterile container by parents at the beginning and at the end of the trial. Immediately, all samples are stored frozen until to be analyzed at the INYTA.

### Adherence and tolerance

Adherence will be measured as a percentage using the following formula:$$ \mathrm{Quick}=\left(\left(\mathrm{Pillsingested}{\textstyle \hbox{-}}\mathrm{pillsreturned}\right)/\mathrm{Pillspredicted}\right)\times 100 $$

These data will also be taken into account for statistical analysis as fixed effects. Tolerance is reported as the descriptive statistics of the adverse effects in relation to the achieved dosage level.

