**Fig. 1 Fig1:**
[figure not shown]
Participant flow diagram. *PPG* pre-pubertal girls; *PPB* pre-pubertal boys; *PG* pubertal girls; *PB* pubertal boys

**Table 1 Tab1:** Distribution of patients according to center

Hospital	Total (160)
Reina Sofía (Córdoba)	20 pre-pubertal girls
	20 pre-pubertal boys
Virgen de las Nieves (Granada)	10 pre-pubertal girls
	10 pre-pubertal boys
	10 pubertal girls
	10 pubertal boys
Clínico Universitario (Santiago de Compostela)	10 pre-pubertal girls
	10 pre-pubertal boys
	10 pubertal girls
	10 pubertal boys
Lozano Blesa (Zaragoza)	20 pubertal girls
	20 pubertal boys

Children are randomly assigned to receive metformin or placebo for six months. Both treatments are administered during meals (to minimize gastrointestinal side effects and the risk of hypoglycemia). The participants’ parents are given a coded vial of pills that contains either metformin or placebo pills for two months. The concealed allocation process ensures that the participants and all investigators are unaware of the allocated treatment. All participants are offered lifestyle intervention advice at all visits.

The clinical hospitals that participate in the RCT form part of the Maternal and Child Health and Development (SAMID network). Moreover, the RCT has been registered in the European Clinical Trials Database on 14 November 2011 (EudraCT, ID: 2010-023061-21).

In accordance with the “International Conference on Harmonization of Technical Requirements for Registration of Pharmaceuticals for Human Use” Guide (ICH): “CPMP/ICH/291/96 Note for Guidance on General Considerations for Clinical Trials,” this is a phase III clinical trial because it involves a commercialized drug for which a new indication that is not included in its technical specifications will be investigated.

The CONSORT statement (Consolidated Standards of Reporting Trials) has been taken into account in the study design report, as well as for the abstract and the flow diagram (Fig. 1), thereby increasing the reporting quality for the RCT. Moreover, the Standard Protocol Items: Recommendations for Interventional Trials (SPIRIT) guidelines for this study protocol are attached in Additional file 1.

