### Statistical analysis

Data will be analyzed using SPSS software version 22 for Windows. Descriptive statistics for all outcomes will be determined. A Kolmogorov-Smirnov test will be used to test data normality. Data that are not normally distributed will be transformed by means of a log10 or square root for analysis. The homogeneity of variances will be determined with a Levene’s test. Normally distributed data will be reported as mean ± standard deviation (SD) and nonparametric data as median (range). The analysis selected to determine the effect of treatment is a linear mixed effects model (LMM), for which the center is considered covariance to adjust the statistical analysis. The fixed effects include time, treatment, adherence, puberty, sex, the interactions *time × treatment*, *time × treatment × puberty* and *time × treatment × sex*. A Bonferroni test will be used to assess the specific differences between the treatments.

Regarding genetic variations, linear regression will be performed to analyze differences in principal variable changes between genotypes and to evaluate independent associated factors.

Moreover, the raw microbiologic data are reported as relative abundances. Differences among times, treatments and puberty are compared using the Mann-Whitney *U* test. Finally, the clustering of the colonic microbiota in both of groups is calculated by a principal component analysis.

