In view of this situation, our research could provide consolidated evidence regarding metformin’s effects on obese children, considering the pubertal stage via homogeneous Tanner stratification, as well as finding possible lines of action by metformin. Nevertheless, the study has several limitations, including the difficulty of assessing treatment compliance in children, as well as lifestyle changes. Moreover, the supervision of dietary habits and physical activity proves rather complicated. We are controlling for medication taken by means of the delivery and return of the bottles; however, we are aware that this strategy does not ensure accuracy regarding intervention compliance information.

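### The printed adherence formula subtracts returned pills from ingested pills, so taken literally it counts returned pills twice and understates adherence whenever pills come back

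*Protocol article*

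**What the plan says.** In the protocol article, Adherence and tolerance, the sentence "Adherence will be measured as a percentage using the following formula" introduces an equation whose left-hand side is labelled *Quick*. Its terms (run together by the equation markup) are "Pillsingested" minus "pillsreturned" in the numerator and "Pillspredicted" in the denominator, multiplied by 100. The section adds that these data go into the statistical analysis as fixed effects. Statistical analysis confirms this: "The fixed effects include time, treatment, adherence, puberty, sex", followed by three interactions, none of which involves adherence.

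On how intake is observed, the Discussion says "We are controlling for medication taken by means of the delivery and return of the bottles" and concedes that the method does not guarantee accurate compliance data. The Interventions section (traceability paragraph after Fig. 2) says the quantity dispensed to each child is recorded. Nowhere does the article define pills ingested differently or give another adherence formula.

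**The concern.** A returned pill is a pill that was not taken. When intake is inferred from what went out and what came back, pills ingested is already net of returns, and subtracting returns again removes them twice. The result is not a percentage of prescribed pills taken: it falls too fast as adherence falls, and it turns negative once more pills are returned than taken.

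Two things are at stake. The first is the adherence figure itself, which will be wrong for every child who returns a pill if sites or analysts follow the formula as printed. The second is the model for the treatment effect, where adherence is a covariate. How far the error reaches the treatment terms has to be worked out, not assumed.

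**Working it through.** The article states no adherence figure, so there is nothing to reproduce. The check is algebra on the printed formula.

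**Inputs**
- I = pills ingested, R = pills returned, P = pills predicted (Adherence and tolerance).
- D = pills dispensed (recorded according to Interventions).
- I = D − R, because intake is tracked by delivery and return of bottles (Discussion).
- For illustration only, P = 360: two tablets a day for about 180 days, an assumption based on "Children are randomly assigned to receive metformin or placebo for six months" and a twice-daily schedule. The percentages depend on D/P, not on 360.

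**Step 1: what the formula computes**

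Printed: A_printed = 100 × (I − R)/P. Substituting I = D − R gives A_printed = 100 × (D − 2R)/P.

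Pill-count adherence: A = 100 × I/P = 100 × (D − R)/P.

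The understatement is A − A_printed = 100 × R/P points. The printed value is negative whenever I < R, that is, when A < 50 × D/P.

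**Step 2: size when D = P = 360 and all untaken pills are returned**

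| True adherence | I | R | Printed formula | (D − R)/P |
|---|---|---|---|---|
| 90 % | 324 | 36 | (324 − 36)/360 = 80 % | 90 % |
| 80 % | 288 | 72 | (288 − 72)/360 = 60 % | 80 % |
| 50 % | 180 | 180 | (180 − 180)/360 = 0 % | 50 % |
| 40 % | 144 | 216 | (144 − 216)/360 = −20 % | 40 % |

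**Step 3: size when more is dispensed than predicted (assumed surplus)**
- 10 % surplus, D = 396: a fully adherent child returns 36 and scores (360 − 36)/360 = 90 %. Scores are negative below 55 % true adherence.
- 20 % surplus, D = 432: a fully adherent child returns 72 and scores (360 − 72)/360 = 80 %. Scores are negative below 60 %.

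**Step 4: what happens in the mixed model**

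Write k = D/P. From Step 1, A_printed = 2A − 100k, so A = (A_printed + 100k)/2. If the model contains a linear term βA, then βA = (β/2) × A_printed + 50kβ. When k is the same for every child, the last term is a constant absorbed by the intercept. The adherence coefficient is halved, and the fit, the treatment term and the time × treatment terms are unchanged. Adherence enters as a main effect only, so this holds even if one arm returns more pills than the other.

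**Step 5: when the rescaling argument fails**
- *k varies between children.* The term 50kβ is then not constant. Illustration, assuming whole containers of 28 (Interventions), one tablet twice daily, and a predicted count that follows the actual visit interval: five containers hold 5 × 28 = 140 tablets, enough for 140/2 = 70 days. A fully adherent child seen at 60 days has P = 120 and R = 20, and scores (120 − 20)/120 = 83 %. A fully adherent child seen at 70 days has P = 140 and R = 0, and scores 100 %. The same behaviour gets different scores. With dispensed minus returned the first child scores (140 − 20)/120 = 100 %.
- *Completeness of returns varies.* If ingestion were known separately and only half the untaken pills came back, a child at 80 % with D = P would score 80 − 10 = 70 %, not 60 %. A mix of complete and incomplete returners is not on one common line. If ingestion is instead derived as D − R, unreturned pills distort the corrected count as well, and the new numerator does not cure that.

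**The case against.** The strongest reply is that this is a wording slip. The trial has no direct measure of ingestion; what it has is a record of pills dispensed and a return of bottles. The working calculation may well be delivered minus returned, which is correct, and the stray label *Quick* on the same line suggests careless drafting rather than a deliberate rule. That is plausible, and the article does not show that anyone will compute dispensed minus twice returned. What stands against it is that the printed line is the only definition of adherence given, and someone who follows it literally gets wrong values.

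The second reply concerns the model. A reader might infer that the error biases the treatment effect, particularly if metformin leads to more returned tablets. The article does not support this. With a common dispensed-to-predicted ratio and all untaken pills returned, the error is an exact linear rescaling, and arm differences in returns do not change the treatment terms (Step 4). Under those conditions a between-arm gap in adherence would be described as twice its true size, but the treatment estimates would be the same.

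Third, a reader might infer that the percentage drives a compliance threshold, an exclusion or a formal compliance report. The article states none of these. Nor is any defect shown in the denominator. These replies limit the point; they do not remove it.

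**Conclusion.** The formula is wrong as printed. On a literal reading it understates adherence by 100 × R/P percentage points: 10 points at 90 % true adherence, 20 at 80 %, 50 at 50 %, with negative scores below 50 %. These figures assume that dispensed equals predicted and that all untaken pills are returned. It is right only for a child who returns nothing.

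The consequence for the main analysis is conditional. The treatment estimates move only if the dispensed-to-predicted ratio or the completeness of returns differs between children. The article neither rules that out nor gives data to size it. Otherwise the only effect in the model is a halved adherence coefficient. All of this depends on the word for ingested being meant literally; if it stands for dispensed, the arithmetic is sound and only the text is wrong. Either way the line needs correcting, but it does not by itself threaten the primary comparison.

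**What to change.** In Adherence and tolerance, replace pills ingested with pills dispensed, so that the definition reads:

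Adherence (%) = (pills dispensed − pills returned) / pills predicted × 100

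and change the left-hand label from *Quick* to *Adherence*. No change to the denominator or the model is needed for this point. If any adherence values have already been computed, confirm which numerator was used and recompute them if it was the literal one.

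The cost is one line of text. Quantities dispensed are already recorded and bottles are already returned, so no new kind of data is required. According to Trial status, recruitment was still under way, so the correction can be made before the analysis.

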### Randomization

The participants are assigned to metformin or placebo in accordance with a randomization schedule generated by the Pharmacy Service of the Virgen de las Nieves University Hospital in Granada, with MAS 100 version 2.1 software (Glaxo-Welcome, Madrid, Spain) by the Support Consortium to Biomedical Research Network (CAIBER). At each center, 50 % of the children are assigned to each group.

The drug presentation format for the metformin and placebo groups has the same appearance. The local physician responsible for the procedure is only aware of the box/bottle codes of the tablets (as well as the registration number of the participating child). These codes have a corresponding equivalent available only to the coordinating investigator who has the other data of pharmaceutical interest, such as the origin, lot number and manufacturing and packaging dates (as well as whether the drug is metformin or placebo). The aforementioned local physician is not aware of these data and thus assigns the participant to one study group, without knowledge of the primary treatment administered.

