### Interventions

The patients are instructed to taking a initial dose of 50 mg twice daily for 10 days, followed by 500 mg twice daily until the end of the treatment. The presentation comprises tablets in opaque, white plastic containers and a side label with 28 units. The dietician centers administer a food frequency questionnaire (FFQ) and a physical activity survey to all participants at the beginning and at the end of the trial. All participants are provided with standardized healthy lifestyle advice at the start of a one-on-one session, including a healthy diet and exercise advice sheet. The participants attend an initial trial baseline visit, followed by three additional visits at 2-month intervals (Fig. 2), which include anthropometric parameter and blood pressure (BP) assessments, as well as a physical examination. A medical history is obtained for each participant, including documentation of the family history.

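### Tolerance is tabulated by achieved dose, which adverse effects can themselves lower; the primary summary should be by randomised arm in all treated children

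*Protocol article*

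**What the plan says.** Under Adherence and tolerance, directly after a pill-count adherence percentage, the protocol article states: "Tolerance is reported as the descriptive statistics of the adverse effects in relation to the achieved dosage level". It does not define achieved dosage level and does not mention treatment arm.

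Three other sections bear on this:

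- Interventions gives one schedule for everyone: a 10-day starting dose, "followed by 500 mg twice daily until the end of the treatment". There are no randomised dose levels.
- Adverse effects and co-medication provides a telephone route: "A contact number is provided to enable enquiries regarding any symptom perceived as adverse". Of those who use it, the article says: "They are also requested to suspend the medication". It gives no duration and says nothing about restarting. The same section sets the safety criterion ("To assess the safety of metformin administration, the primary evaluation criteria are the absence of the adverse effects (AEs) described") and provides for collection in everyone ("The patients are assessed regarding all symptoms at each visit to identify potential AEs"). Onset date, severity, relation to medication and action taken are recorded.
- Interim analyses and stopping rules says that the data of withdrawn participants are left out of the statistical analysis.

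Allocation is balanced: "At each center, 50 % of the children are assigned to each group". Statistical analysis promises that "Descriptive statistics for all outcomes will be determined" but names no comparison of adverse effects.

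**The concern.** Because the planned dose is the same for all, children's achieved intake differs only through what happens after randomisation: missed tablets, suspension or stopping. The suspension request links adverse effects to that variable. A child who has a symptom, phones and stops moves from the full-dose row to a lower one and takes the adverse effect along. The table then groups children by a possible consequence of the event it describes, and full-dose metformin can look better tolerated than it is.

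The grouping also has no clear meaning in the placebo arm, where tablets taken carry no metformin. Several of the listed events (cold or flu, pharyngitis, otitis, headache) are ordinary childhood illness. Only the blinded comparison with placebo separates these from drug effects, and the stated summary does not use it. What is at stake is the tolerability evidence in children aged 7–14. The efficacy analysis is not affected.

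**Working it through.** The article gives no adverse-effect rate, no share of children suspending and no length of suspension, so there is no figure of its own to reproduce. All rates below are assumptions, used to show direction and range.

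**1. Simple illustration, no true dose effect.** Let p be the adverse-effect rate, s the share of affected children who suspend and end with low intake, and b the share with low intake for unrelated reasons.

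- Low intake among affected children: s + (1 − s)b. Among the others: b.
- Take p = 0.30, s = 0.50, b = 0.15. Low intake among the affected is 0.50 + 0.50 × 0.15 = 0.575.
- Low-dose row: 0.30 × 0.575 = 0.1725 with an adverse effect and 0.70 × 0.15 = 0.105 without. Rate = 0.1725 / 0.2775 = 62%.
- Full-dose row: 0.30 × 0.425 = 0.1275 with and 0.70 × 0.85 = 0.595 without. Rate = 0.1275 / 0.7225 = 18%.
- Spurious ratio: 0.622 / 0.176 = 3.5.
- Over s = 0.25–0.75 and b = 0.10–0.25, the ratio runs from 1.76 (s = 0.25, b = 0.25) to 7.94 (s = 0.75, b = 0.10).

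This assumes that every suspension is long enough to put the child in the low-dose row, so 1.76 is not a lower bound.

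**2. Simulation with a true dose effect and varying suspension.** There were 80,000 children per scenario, followed for 180 days. Intended adherence was uniform on 50–100%. The six-month adverse-effect risk at zero dose was 15%, with a hazard ratio (HR) of 1, 2 or 4 for full against zero dose. Rates are tabulated at achieved intake below 75% against 75% or more, with suspended children kept in the table.

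| Suspension | Share suspending | HR 2: low vs high | HR 4: low vs high |
|---|---|---|---|
| None (true direction) | 0% | 22 vs 26% | 32 vs 42% |
| Permanent | 10% | 24 vs 24% | 34 vs 40% |
| Permanent | 25% | 26 vs 21% | 38 vs 37% |
| Permanent | 50% | 30 vs 16% | 43 vs 29% |
| 7 days | 50% | 23 vs 25% | 33 vs 41% |
| 7 days | 100% | 25 vs 24% | 35 vs 39% |
| 14 days | 50% | 24 vs 23% | 35 vs 40% |
| 14 days | 100% | 27 vs 21% | 38 vs 36% |

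With no dose effect (HR 1) and 50% suspending permanently, the table shows 20 vs 9%. In every scenario with suspension, the low-against-high contrast moves toward an inverse relation. Whether it ends attenuated, flat or reversed depends on the inputs.

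**3. If suspended children are treated as withdrawn and excluded** (50% suspending), the direction is kept: 12 vs 15% at HR 2 and 20 vs 27% at HR 4. But the overall adverse-effect rate falls from 24% to 14% and from 37% to 23%. The error is then undercounting.

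**4. Check on the remedy.** Grouping by intended adherence, which an adverse effect cannot alter, keeps the true direction (22 vs 26% and 32 vs 42%). Randomised arm has the same property, provided children who stop are kept in.

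**The case against.** A reader might infer that the planned table will show the dose relation reversed. The documents do not support that. The suspension request is described only for those who use the contact number, and its length is not given. A pause of 7 to 14 days in about 180 costs 7/180 = 4% to 14/180 = 8% of intake, and most of the short-pause scenarios above are attenuated or about flat. If withdrawn children are left out, the direction is preserved. This objection stands, and the claim is limited to a bias whose size is unknown.

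A reader might also infer that the trial will give no metformin-versus-placebo comparison of adverse effects. That would be an argument from silence. The article promises descriptive statistics for all outcomes, sets a separate safety criterion, and may leave table layouts to a full protocol or SAP that is not shown. This stands too: a by-arm table is not stated, but it is not ruled out.

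Third, achieved dosage level is undefined and could mean the step of the schedule a child was on when the event occurred. That reading largely avoids the bias. However, the sentence directly follows the pill-count formula, so intake over the trial is at least as natural a reading. If the phrase means the highest step reached, an early event can still hold a child at the lower step.

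Finally, the summary is only descriptive and no dose-toxicity inference is announced. That limits the harm. It does not remove the defect, because the article fixes this grouping as its report of tolerance and readers will compare the rows.

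**Conclusion.** The concern holds in a limited form. The one tolerance summary the article specifies uses a post-randomisation grouping that adverse effects can lower, if achieved dose means intake over the trial. With suspended children kept in, the table is biased toward an inverse relation: a spurious ratio of 1.8 to 7.9 in the simple illustration with no dose effect, and anything from slight attenuation to clear reversal when a real dose effect is assumed. With suspended children excluded as withdrawals, the distortion is an undercount, for example 14% against 24%. These figures all rest on assumed rates. On either handling the table cannot be read as a dose-toxicity relation, and it leaves unused the randomised contrast that the design provides. The sponsor should change the sentence.

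**What to change.** Replace the tolerance sentence with wording such as: *Tolerance is summarised by randomised arm, in all children who took at least one tablet, as the number and proportion with each adverse effect and with suspension or discontinuation because of it.* State in the same place that the exclusion of withdrawn participants under Interim analyses and stopping rules does not apply to safety data.

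If a dose-related description is still wanted, make it secondary, define the term, and use the dose being taken at event onset, since the onset date is already recorded. State that it is not to be read as a dose-toxicity relation. One reason is that time at each step is very unequal, at 10 days against roughly 170 of 180.

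The cost is a few sentences and re-cut tables from data already being collected. The metformin arm may look less well tolerated than in the planned table. No change to the dose or to the suspension request is proposed.
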